### Data collection

Data will be collected into an Microsoft Access data base designed to capture initial visit information and generate a consultation note. Baseline data and ongoing data collection as outlined in Table 4 will be obtained.

**Table 4 T4:** Baseline and ongoing data collection

Baseline data:
• Blood pressure will be measured at each visit using the BpTru (VSM Technologies, Vancouver, Canada)
• serum creatinine.
• U/S abdomen for renal size and Doppler presence of renal artery stenosis
• Percent function of both kidneys and change with captopril on renal scan
• MR/CT angiography to determine presence or absence of renal artery stenosis
• Med review
• allergies
• Past surgery, hospitalizations
• Initial History and physical
• Labs, urine/blood
• ECG
Follow-up lab data: every 3 months
• Urea and creatinine
• Lipids q6 months
• U/S annually for renal size

### Patient follow-up procedures

Any patient randomized to medical therapy who has an indication for revascularization will have attempted further medical management for another 3 months. Patients randomized to revascularization who have an indication will be offered revascularization. All patients will be followed prospectively for both an intent to treat and per protocol analysis. The analysis will also be carried out stratified by the result of the renal resistance index (normal vs abnormal) to determine it's prognostic ability.

The decision to proceed toward revascularization will be based on a rise in creatinine by > 20% per year from baseline for year one and in year 2, by > 20% over the average creatinine from year one. To reduce the possibility that the rise in creatinine is temporary, due for example to a hypovolemic event, a repeat creatinine will be required from 3 days to 3 months later to confirm that the creatinine has risen by 20%. If an ACEi or ARB has been started after enrollment into the study, a rise in creatinine of 20% in the first 3 months after the initiation will be permitted. The creatinine trigger for revascularization after ACEi or ARB is started will be a creatinine rise of 40% during that year. The blood pressure trigger for revascularization will be systolic blood pressure ≥ 150 mmHg and/or diastolic blood pressure ≥ 95 mmHg on any visit.

Patients randomized to the medical management group will not be excluded from revascularization. If blood pressure is ≥ 170 mm Hg and/or diastolic blood pressure ≥ 100 mm Hg on any visit despite treatment with at least three antihypertensives at maximal dosage patients can be referred for revascularization. In this circumstance, patients will continue to be assessed in an intent-to-treat analysis. If the creatinine doubles from baseline patients can be referred for revascularization.

### Study withdrawal

Patients will be censored and withdrawn from follow-up at their request. Patients will be censored at the time they reach an endpoint including the need for renal replacement therapy, death or doubling of the creatinine from baseline.

### Statistical analysis

This is a pilot study. The expected number of patients enrolled and time-frame of the study will allow an appropriate sample size calculation for a large multicentered study. The goal is to recruit 20 patients with renal vascular disease. Over the study period, 20% of these are expected to have indications for revascularization. Radermacher found that 20% of patients with ARVD had RRI ≥ 80 but it is likely that a greater fraction of those who require revascularization will have a high RRI[16]. It is estimated that this will be 1/3 in this study. This should lead to enough patients in each group to gather meaningful information to plan a larger study.

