### Identification of eligible patients

Patients referred to a renal vascular clinic in an academic health sciences center will be eligible to enter the study. This clinic is devoted to the diagnosis and management of renal vascular disease. After referral, patients have a minimum data set of screening laboratory and diagnostic tests and screening diagnostic tests including a renal ultrasound, Doppler of the renal arteries and RRI. At the baseline visit after collecting appropriate history physical examination and lab data to document the risk factors signs and symptoms of ARVD all the tests are reviewed. If the patient has an intermediate or high probability for revascularization based on a clinical assessment of the history, physical, lab and screening tests, an MR angiogram or CT angiogram is arranged. All patients receive aggressive medical management aimed at cardiovascular and renal risk reduction with a focus on blood pressure and lipid control and use of (Acetyl-salicylic acid) ASA. In this protocol, patients assessed at the baseline visit who are diagnosed with ARVD will be asked to consent to this study. Randomization to revascularization or medical management will take place later for those patients that develop indications for revascularization. All patients with renal vascular disease are followed at three month intervals. Following revascularization, patients are seen monthly for six months. Patients enrolled in the study will be receiving appropriate medical care according to clinical practice guidelines and will be considered part of regular clinical practice. No additional tests or procedures other than the consent to participate in a study, will be performed on those participating in this study.

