### Sample size considerations

At the time the study was planned, it was expected that the renal vascular clinic would take in an expected 240 patients over 1.5 years. During this time at least 20% of the patients are expected to have an indication for revascularization. The minimum follow-up for those getting revascularized will be 6 months and the maximum possible 24 months. Based on the previous studies by Radermacher, 20% of subjects with ARVD will have RRI ≥ 80[24]. It is unknown what fraction of those who have an indication for revascularization will have an RRI ≥ 80 but it is likely greater than 20%. An estimate of 1/3 of the revascularization group will be used. The numbers are likely to distribute as seen in Table 5. The purpose of the pilot is in part to determine this distribution of patients so that a large randomized study can be planned.

**Table 5 T5:** Expected distribution of patients in study according to RRI status and need for revascularization assuming 240 patients screened

Total patients	240			
Requiring Renal revascularization	Yes (20%) 48		No (80%) 192	
RRI (estimated) N	< 80 (2/3) 32	≥ 80 (1/3) 16	< 80 (2/3) 128	≥80 (1/3) 64
Randomized to revascularization	Y/N 16/16	Y/N 8/8		

In the DRASTIC study, with follow up for one year, 8% of those randomized had elevations of creatinine by at least 50% [28]. The patients in the RAVE study are likely to have a greater rate of progression to end points as they will be a more severe group with ARVD. The DRASTIC study randomized to revascularization, all patients with renal vascular lesions > 50% with diastolic blood pressure > 95 mmHg on only 2 medications. Thus patients with isolated systolic hypertension or patients who would have responded to 3 or more medications were excluded in that study. Recruitment of patients for renal vascular disease can be difficult as demonstrated by the ongoing CORAL study with fewer than 25% enrolled more than 50% into the planned enrollment period. Indeed, in the first six months of enrollment fewer patients were seen in clinic than expected (40 vs 80) and less than 10% of these had indications for revascularization.

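### The recruitment goal of 20 implies about 4 randomised patients while Table 5 shows 48, so the claim that numbers will suffice to plan a larger trial is unsupported

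*Protocol article*

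**What the plan says.** Two sections of the protocol article describe the size of the study.

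- **Statistical analysis.** The target is given as "The goal is to recruit 20 patients with renal vascular disease". On indications it says "Over the study period, 20% of these are expected to have indications for revascularization". For the share of those patients with RRI ≥ 80 it says "It is estimated that this will be 1/3 in this study". It concludes: "This should lead to enough patients in each group to gather meaningful information to plan a larger study".
- **Sample size considerations.** This section starts from 240 patients entering the clinic over 1.5 years, an expectation dated to the planning stage, with at least 20% indicated. On RRI it says "An estimate of 1/3 of the revascularization group will be used", after citing 20% for patients with atherosclerotic renal vascular disease (ARVD) and remarking that the share among indicated patients is probably higher. Table 5 is titled "Expected distribution of patients in study according to RRI status and need for revascularization assuming 240 patients screened", and the text presents it as the probable split. The section ends by reporting that in the first six months "fewer patients were seen in clinic than expected (40 vs 80) and less than 10% of these had indications for revascularization".

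Identification of eligible patients settles who is randomised: "Randomization to revascularization or medical management will take place later for those patients that develop indications for revascularization".

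**The concern.** The two sections use the same proportions but start from 20 and from 240, so they imply very different trials. The 20% is applied once to recruited patients with renal vascular disease and once to everyone screened in the clinic. These are different populations, because referral to the clinic comes before the diagnosis. A reader cannot tell which number the study is working to, or whether the target counts screened, recruited or randomised patients.

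This matters because the pilot's declared product is information for sizing a multicentre trial. Study aims sets the primary objective as the frequency of death, dialysis or doubling of creatinine in randomised patients, and Primary outcome stratifies it by RRI. If the goal of 20 is the operative number, the arm-by-RRI cells that Table 5 displays will be nearly empty.

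A smaller fault lies in the same table. Its column for patients without an indication uses a high-RRI share that the text does not give for them.

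**Working it through.** **Inputs.** Goal 20, share indicated 20% and high-RRI share 1/3 (Statistical analysis). Intake 240 over 18 months, share indicated 20%, high-RRI share 1/3 for the revascularization group and 20% for ARVD overall, and early experience of 40 seen against 80 expected with under 10% indicated (Sample size considerations). Allocation is 1:1 (the cells of Table 5).

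**Formulas.** Randomised = N × share indicated. High RRI = randomised × 1/3. Per arm = half of each.

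**1. Table 5 reproduces from 240.** 240 × 0.20 = 48. Of these, 48 × 2/3 = 32 (16/16) and 48 × 1/3 = 16 (8/8). The remaining 192 are split 192 × 2/3 = 128 and 192 × 1/3 = 64.

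**2. The same arithmetic from the goal of 20.**

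| | Goal of 20 | Table 5 (240) |
|---|---|---|
| Randomised | 4 | 48 |
| Per arm | 2 | 24 |
| RRI < 80, per arm | 1.33 | 16 |
| RRI ≥ 80, per arm | 0.67 | 8 |

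The ratio is 48/4 = 12. Reaching 48 randomised at 20% needs 48/0.20 = 240 recruited.

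**3. Chance does not close the gap.** With the number indicated distributed as Binomial(20, 0.20), the probability of 8 or more is about 3%, and of 10 or more about 0.3%. With 4 randomised, the probability that none has RRI ≥ 80 is (2/3)^4 = 20%. The probability of at most one is 0.198 + 4 × (1/3) × (2/3)^3 = 59%.

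**4. Precision.** For 0 events in n patients, the exact 95% upper limit is 1 − 0.025^(1/n).

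- n = 2: 84%
- n = 6: 46%
- n = 24: 14%

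The event count is held at 0 so that the limits are comparable.

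**5. Early accrual.** 240 over 18 months is 80 per six months, which matches the expected 80. At the observed 40 per six months, 18 months gives 40 × 3 = 120. If under 10% remained the indicated share, fewer than 120 × 0.10 = 12 would be randomised, fewer than 6 per arm. If the share later rose to the planned 20%, the figure would be 120 × 0.20 = 24. Both are scenarios that rest on the intake staying at its early level. Neither matches 4 or 48.

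**6. High-RRI share in the column without an indication.** Table 5 puts 64/192 = 33.3% there and 16/48 = 33.3% among the indicated, so (16 + 64)/240 = 33.3% overall. The text gives 20% for ARVD overall and expects a higher share among the indicated. The table shows no difference between the columns.

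**The case against.** The best defence is that 240 is not a rival target. The text dates it to the planning stage, the table title states its assumption, and the shortfall is disclosed. The 20 may be a goal set later in view of slow intake, and it counts recruited patients, not screened ones. This is a fair account of how both numbers might arise, and it means that the fault is an unreconciled projection with an unclear denominator. It does not remove the fault. The article nowhere says that the 20 replaces the projection, it still offers Table 5 as the likely distribution, and it applies 20% to both bases. Even if 20 meant patients randomised, it would not agree with 48.

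Randomization and study blinding can also be read as assigning every consenting patient, with the envelope left sealed. Even so, the treatments differ only for those with an indication, about 4.

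Four stronger readings are tempting but go too far.

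- **That the adequacy statement is false.** The article sets no numerical criterion for enough, and some feasibility outputs (intake, share indicated) could still be learned, if imprecisely. Moreover, Primary outcome words the objective for patients with ARVD, not only the randomised. On that reading all 20 contribute to a pooled frequency, and 0/20 has an upper limit of 1 − 0.025^(1/20) = 17%. Unsupported is the right word.
- **That fewer than 12 is a forecast.** The rate under 10% comes from the first six months, whereas the 20% refers to the whole study period and indications develop during follow-up. It is one scenario.
- **That the column without an indication should read 160 and 32.** Those values require the ARVD figure of 20% to hold for all 240 screened (0.20 × 240 − 16 = 32), which the text does not say. It shows only that 1/3 is unexplained there. These patients are not randomised, so no arm size changes.
- **That comparisons by arm or by RRI should be barred.** They are stated secondary objectives. Small numbers argue for describing them cautiously, not for deleting them.

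**Conclusion.** The point holds in this form. The stated goal implies about 4 randomised patients and Table 5 shows 48, a twelvefold difference produced by applying the same 20% and 1/3 to 20 recruited and to 240 screened patients. The table was not revised for the reported early shortfall, and its high-RRI share for patients without an indication is at odds with the text. At about 2 per arm, and 0.67 per arm with RRI ≥ 80, the article gives no basis for saying that each group will be informative for planning.

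The figure of 4 rests only on the article's own goal and percentage. The scenarios of fewer than 12 and of 24 randomised rest on extrapolating six months of intake, and should be read that way. The error should be corrected because the study's size, on which its declared purpose depends, cannot be determined from the text as it stands.

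**What to change.** 1. State one target and say whether it counts patients screened, recruited or randomised. Apply the 20% to that base only.
2. Recompute Table 5 from that target, or label it as the superseded planning projection. Beside it, show the early accrual as a scenario with its assumption: about 120 seen and fewer than 12 randomised if the first-six-month rates persisted, with a note that later indications could raise this.
3. Make the high-RRI share in the column without an indication consistent with the text, or justify 1/3 there.
4. Replace the adequacy sentence with the precision expected at the restated number, such as the width of the exact interval for the event proportion per arm and pooled.
5. Keep the secondary objectives, but describe between-arm and RRI-by-arm results as descriptive at that size.

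The cost is a revision of text and one table. No extra patients are needed. The downside is that the stated expectations become less favourable.

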### Sample size considerations

At the time the study was planned, it was expected that the renal vascular clinic would take in an expected 240 patients over 1.5 years. During this time at least 20% of the patients are expected to have an indication for revascularization. The minimum follow-up for those getting revascularized will be 6 months and the maximum possible 24 months. Based on the previous studies by Radermacher, 20% of subjects with ARVD will have RRI ≥ 80[24]. It is unknown what fraction of those who have an indication for revascularization will have an RRI ≥ 80 but it is likely greater than 20%. An estimate of 1/3 of the revascularization group will be used. The numbers are likely to distribute as seen in Table 5. The purpose of the pilot is in part to determine this distribution of patients so that a large randomized study can be planned.

**Table 5 T5:** Expected distribution of patients in study according to RRI status and need for revascularization assuming 240 patients screened

Total patients	240			
Requiring Renal revascularization	Yes (20%) 48		No (80%) 192	
RRI (estimated) N	< 80 (2/3) 32	≥ 80 (1/3) 16	< 80 (2/3) 128	≥80 (1/3) 64
Randomized to revascularization	Y/N 16/16	Y/N 8/8		

In the DRASTIC study, with follow up for one year, 8% of those randomized had elevations of creatinine by at least 50% [28]. The patients in the RAVE study are likely to have a greater rate of progression to end points as they will be a more severe group with ARVD. The DRASTIC study randomized to revascularization, all patients with renal vascular lesions > 50% with diastolic blood pressure > 95 mmHg on only 2 medications. Thus patients with isolated systolic hypertension or patients who would have responded to 3 or more medications were excluded in that study. Recruitment of patients for renal vascular disease can be difficult as demonstrated by the ongoing CORAL study with fewer than 25% enrolled more than 50% into the planned enrollment period. Indeed, in the first six months of enrollment fewer patients were seen in clinic than expected (40 vs 80) and less than 10% of these had indications for revascularization.

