### Study interventions

The intervention is assignment to a group receiving medical therapy alone. The standard of care currently for patients with renal artery stenosis and an indication for revascularization is to have revascularization. Medical therapy includes aggressive blood pressure lowering to target (< 140/90 mm Hg and < 130/80 mm Hg for those with diabetes), LDL reduction < 2.0 with statin therapy, use of ASA or other antiplatelet therapy, diabetes control, diet, exercise and smoking cessation. Referral for diabetes education and management if appropriate.

Percuateneous transluminal renal angioplasty, involves percutaneous access to the arterial circulation using the Seldinger technique at the level of the femoral artery and the passing of an angiographic wire into the renal artery and proximal aorta for contrast dye injection. Patients are admitted to the nephrology ward the day of the procedure and are discharged the following day after lab work has been completed and reviewed. Antihypertensives are given at half dose on the day of the procedure to prevent symptomatic hypotension. ASA is held the day of the procedure. For those on coumadin, it is held 5 days before and vitamin K 1 mg administered and a normal INR is required prior to the procedure. Stenting will be performed at the discretion of the angiographer. Angioplasty of the renal artery with stenting leads to lower restenosis rates and longer term patency [27]. While it seems logical that this greater patency would lead to improved blood pressure control and preservation of renal function, no study has yet been conducted to prove this.

The choice of balloon size, angiographic method and need for stent will be determined on a case by case basis by the angiographer. In general stents are used for those patients with ostial lesions. Renal revascularization to date has not demonstrated in most patients in blood pressure control and has shown no benefit in renal preservation. The DRASTIC study, the largest study to investigate the effectiveness of a revascularization strategy for ARVD had to screen over 1200 patients referred with resistant hypertension to find 543 who received angiography for diastolic blood pressure ≥ 95 mm Hg. Of these, 169 (30%) were found to have renal artery lesions ≥ 50% [28]. The DRASTIC study did not use renal stenting and did not preselect patients using the RRI. Patients that require surgical revascularization will be withdrawn from the study.

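### The 20% indication rate is applied to two different denominators, and Table 5 has no diagnosis step, so its 48 randomised (8 per arm with RRI ≥ 80) does not agree with the protocol's own text

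*Protocol article*

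**What the plan says.** **Sample size considerations.** The base is clinic intake: "it was expected that the renal vascular clinic would take in an expected 240 patients over 1.5 years". The indication rate follows directly: "During this time at least 20% of the patients are expected to have an indication for revascularization". Table 5 is captioned "Expected distribution of patients in study according to RRI status and need for revascularization assuming 240 patients screened". It divides the 240 into 48 with an indication and 192 without, then divides the 48 by RRI and by arm (16/16 and 8/8). The section closes with early experience: "fewer patients were seen in clinic than expected (40 vs 80) and less than 10% of these had indications for revascularization".

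**Statistical analysis.** The base is different: "The goal is to recruit 20 patients with renal vascular disease. Over the study period, 20% of these are expected to have indications for revascularization". The section concludes that each group should be large enough to inform the planning of a bigger trial.

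**Identification of eligible patients.** Referred patients have screening tests, which include the RRI. Those judged at intermediate or high probability go on to MR or CT angiography, and "patients assessed at the baseline visit who are diagnosed with ARVD will be asked to consent to this study". Randomisation follows later, once an indication develops. Study design and setting likewise randomises only patients with stenosis on angiography and an indication.

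**Yields quoted from elsewhere.** The Background gives a prevalence of 20–40% in severe or resistant hypertension. Study interventions describes an earlier revascularization trial that screened over 1200 referred patients, of whom 543 had angiography: "Of these, 169 (30%) were found to have renal artery lesions ≥ 50" percent of the lumen.

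**The concern.** The same percentage is used once per clinic patient and once per patient with confirmed disease. The eligibility pathway makes these different groups, since not every referral reaches angiography and only diagnosed patients are asked to consent. Table 5 passes from screened patients to randomised patients in one step, under a caption that refers to both patients in the study and patients screened.

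Table 5 is the only place that shows expected numbers by arm and RRI stratum, and it is the visible support for saying that group sizes will be adequate. The pilot is meant to supply planning inputs for a multicentre trial, and the share of referrals with confirmed disease is one of them. If that step stays out of the projection, the screening effort for the larger trial could be understated.

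**Working it through.** **1. Reproduce Table 5.** Inputs: 240 patients, 20% with an indication, 1/3 with RRI ≥ 80, equal allocation.
- 240 × 0.20 = 48
- RRI < 80: 48 × 2/3 = 32, or 16 per arm
- RRI ≥ 80: 48 × 1/3 = 16, or 8 per arm

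The table reproduces exactly. Its arithmetic is sound; the question is what the 20% is a percentage of.

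**2. Compare the two denominators.** Let y be the share of clinic patients with confirmed ARVD.
- 20% among diagnosed patients: randomised = 240 × y × 0.20. This equals 48 only at y = 1.
- 20% per clinic patient: randomised = 48 for any y, but the rate among diagnosed patients is then 0.20/y. This equals the 20% in Statistical analysis only at y = 1.

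On either reading, one of the two sections needs correcting unless every referral has ARVD.

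**3. Size if the 20% applies to diagnosed patients.** The clinic's own y is not given. The values below are assumptions taken from other populations described in the article.

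| Assumed y | With ARVD | Randomised | Table 5 too large by | Per arm, RRI < 80 | Per arm, RRI ≥ 80 |
|---|---|---|---|---|---|
| 1.00 | 240 | 48 | 1 | 16 | 8 |
| 0.40 | 96 | 19.2 | 2.5 | 6.4 | 3.2 |
| 0.31 (169/543) | 74.7 | 14.9 | 3.2 | 5.0 | 2.5 |
| 0.20 | 48 | 9.6 | 5.0 | 3.2 | 1.6 |

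If the 20% is instead per clinic patient, the implied rate among diagnosed patients is 0.20/0.40 = 50% at the upper prevalence figure and 0.20/0.20 = 100% at the lower one.

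**4. Projection from the early data.** This needs no borrowed yield. It assumes that intake and the indication rate stay as seen in the first six months.
- Intake: 40 × 3 six-month periods = 120, half of the planned 240
- Randomised: below 120 × 10% = 12, against 48, so Table 5 is more than 4 times larger
- A factor of 2 comes from intake, and more than a factor of 2 from the indication rate (20% against under 10%)
- RRI ≥ 80 per arm: fewer than 12 × 1/3 ÷ 2 = 2

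**5. Projection from the recruitment goal.** 20 × 0.20 = 4 randomised. With RRI ≥ 80: 4 × 1/3 ≈ 1.3 across both arms.

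**6. What such cells can estimate.** The exact 95% interval for an event proportion is 16–84% for 4 of 8, and 1–99% for 1 of 2.

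**The case against.** The strongest reply is that Sample size considerations can be read as a rate per clinic patient with diagnosis already absorbed. Referrals without ARVD then sit in the 192 with no indication, and 48 stands. RRI fractions for all 240 do not count against this, because the RRI is among the screening tests done after referral. The early-data sentence also uses clinic patients as its base. This reading is available and stands. A reader might infer that the article treats all 240 referrals as confirmed cases, but it nowhere says so. What the reading does not do is reconcile Table 5 with Statistical analysis, where the 20% is explicitly a share of patients with renal vascular disease.

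A reader might also infer that Table 5 is inflated by a fixed 2.5 to 7 times. The documents do not support this. The yields come from resistant-hypertension populations, whereas this clinic is dedicated to renal vascular disease and may do better. The upper end would come from 169/1200 = 14% (a factor of 7.1). That is not a diagnostic yield: only 543 had angiography, and nothing shows that the other 657 or more were free of stenosis.

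Nor does the six-month count show that yield is low. Under 10% of 40 means at most 3 patients, which would have probability 0.028 at a rate of 20%. But the 20% is expected over the study period and indications can arise later, so the comparison is not like for like. It cannot separate low yield from delayed or infrequent indications.

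Finally, the article itself reports the shortfall and says that the pilot exists partly to learn this distribution. That is fair and lowers the seriousness. Even so, Table 5 and the statement about adequate group sizes were left unrevised beside those data.

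**Conclusion.** The inconsistency is established: one rate, two denominators, and no diagnosis or consent row between 240 screened and 48 randomised. Its size is conditional. The factor is 1 if the 20% is truly per clinic patient, in which case Statistical analysis must change. It is about 2.5 to 5 if the 20% applies to diagnosed patients and the yield is 20–40%, a range borrowed from other populations.

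The firmer check is the clinic's own experience, which projects fewer than 12 randomised if intake and indication rate persist, with the caveat that indications may still accrue. The goal of 20 patients projects about 4. These lower projections give from under 1 to about 3 patients per arm with RRI ≥ 80, not 8, and do not support the claim of enough patients in each group. This should be corrected. It does not undermine the pilot's feasibility purpose.

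**What to change.** - State one denominator for the 20% and use it in both Statistical analysis and Sample size considerations.
- Rebuild Table 5 as a cascade: clinic patients screened, ARVD confirmed, indication, RRI stratum, arm. Show the assumed yield as an assumption with a range.
- Restate the expected number randomised from the clinic's observed intake and indication rate, noting that follow-up is incomplete.
- Replace the statement on adequate group sizes. Say that the pilot will estimate the cascade proportions (yield, indication rate, share with RRI ≥ 80) and the pooled event frequency, each with an exact interval, and that results by arm within RRI stratum are descriptive only.

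This needs one revised table and changes of wording, with no extra patients or tests. The price is that the stated expected numbers become less favourable and the stratified results, although still reported, carry less weight as planning inputs.
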